As actions controlled by the impulsive system often occur outside the individual’s awareness and in responses to well-learned cue-response pairings, it is difficult to override and change such actions i.e. to break the cue-response link. It often takes considerable self-control or capacity to inhibit responses to overcome the automated link. From the perspective of the strength model, self-control, that is the capacity to inhibit the automated response, is a limited resource permitting individuals to inhibit their responses for a finite period until the resource becomes depleted limiting subsequent capacity for inhibition. An important feature of the self-control ‘resource’ is that it is ‘domain general’ i.e. it is a generalizable resource that enables individuals to control their behavior in multiple domains. This has been shown in many studies in which individuals engaged in a task that requires them to inhibit their self-control in one domain results in impaired response inhibition in another. Importantly in the current context, exerting self-control on laboratory-based tasks that require the inhibition of responses leads to reduced capacity to inhibit responses when presented with tempting behaviors in health-related domains such as resisting alcohol in social drinkers or tempting foods in people with low eating restraint. Consistent with this line of research, studies have revealed that training on tasks that require self-control i.e. the ability to inhibit responses will improve response inhibition capacity and provide individuals to inhibit cue-response pairings more effectively. And this effect also appears to be domain general, consistent with the strength model [78] and the reflective-impulsive model [97]. Training on self-control tasks which require regular inhibition of a pre-potent response is, therefore, hypothesised to improve generalized capacity for self-control as shown in previous studies [84,88]. With individuals who have sufficient motivation to reduce their alcohol intake, improving response inhibition capacity is expected to improve capacity to inhibit the temptation to drink. This may be relevant in situations where they may be tempted to drink more than usual. They can therefore bring their improved generalized capacity to bear on reducing their alcohol consumption is situations where they may be tempted to drink to excess. Their additional response inhibition capability afforded to them by virtue of the training would provide sufficient capacity to override the automatic, cue-driven response to stimuli to drink alcohol.

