
We therefore propose that self-control training will only have a substantive effect on behavioral outcomes if individuals are motivated to change their behavior. Participants whose self-control capacity has been trained, but have little or no motivation to reduce their alcohol consumption are less likely to direct the increased self-control capacity gleaned from training toward that particular behavior. They may direct their efforts toward behaviors to which they are more motivated instead. We therefore expect that the combined manipulation of self-control training and motivational imagery-based intervention components, namely, mental simulations, to be more effective in changing behavior than either of the components alone. Importantly, the factorial design adopted in the present study permits the evaluation of the independent and synergistic effects of each of the intervention components on alcohol consumption. In addition, we expect the intervention to be highly acceptable for use in public health promotion campaigns due to its low response burden and highly practical, accessible, and cost-effective means of delivering the intervention.

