We will also conduct mediation analyses to evaluate the effectiveness of the intervention components on alcohol consumption. This will be conducted using moderated linear regression analyses with indirect effects reproduced using Preacher, Curran, and Bauer’s [110] asymptotic bootstrapped algorithms and the bias-corrected bootstrap confidence interval to assess the statistical significance of the effects [111]. Specifically, we will develop binary dummy-coded variables to represent the effects of the mental simulation (1 = received mental simulation, 0 = received irrelevant visualization strategy) and self-control training (1 = received challenging Stroop task, 0 = received easy Stroop task) interventions with an additional variable computed to represent the interaction of the two. The primary outcome variable, follow-up alcohol consumption, will be regressed on these coded variables in the first instance to ascertain direct effects. This will be followed by analyses including multiple mediators of the effects including residualized change scores for the baseline and follow-up measures of the theory of planned behavior variables (intentions, subjective norms, attitudes, perceived behavioral control) and motivation as mediators of the mental simulation intervention and residualized change scores in state perceived self-control between baseline and follow-up as a mediator of the effect of the self-control training intervention. The unstandardized effects and confidence intervals will be used as input for Preacher et al.’s [110] bootstrapped algorithm computational tool to compute the indirect effects. We predict statistically-significant, medium-sized multiple mediation of the effects of the mental simulation intervention on follow-up alcohol consumption by the theory of planned behavior and motivational change scores and significant mediation of the effect of self-control training on alcohol consumption by state self-control change scores. Trait self-control will be included in the analyses as a control variable.

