The research will make a unique contribution to knowledge regarding interventions to reduce alcohol consumption and binge drinking occasions in undergraduate students because it will (a) address the limitations of previous research using multiple intervention techniques concurrently by identifying the unique and interactive effects of two isolated and independent intervention techniques (mental simulation and self-control training) to reduce alcohol consumption through the use of a factorial design [20,112]; (b) assist in identifying the mechanisms behind motivational and self-control training components and their interaction on alcohol consumption by testing the effects of key proposed mediating variables [18]; (c) adopt methods that allow for the efficacy of the intervention to be evaluated including written responses to the mental simulation motivational intervention [108] and using an objective means to manage compliance with the programme of self-control resource training via an online training task [85]; and (d) extend knowledge of the causal effects of an intervention aimed at affecting *change* in health behavior through motivational and self-control related variables beyond that which can be inferred from correlational [113] and panel [114] designs.

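### The listed mediation model gives state self-control one common slope on drinking, so it cannot show that self-control carries the simulation-by-training interaction

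*Protocol article*

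**What the plan says.** **The theory** (protocol article, The current research). "We therefore propose that self-control training will only have a substantive effect on behavioral outcomes if individuals are motivated to change their behavior". Trained participants who lack motivation "are less likely to direct the increased self-control capacity gleaned from training toward that particular behavior". In motivated people, "improving response inhibition capacity is expected to improve capacity to inhibit the temptation to drink". The Background section on the strength model argues in the same way. Training raises a general capacity, and motivation decides where it is spent.

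**The model** (Data analysis). The mediation analysis is introduced with "This will be conducted using moderated linear regression analyses". The terms are then spelled out: a 0/1 indicator for each component, "with an additional variable computed to represent the interaction of the two", change scores for the planned-behavior variables and motivation as mediators of simulation, "residualized change scores in state perceived self-control between baseline and follow-up as a mediator of the effect of the self-control training intervention", and trait self-control as a control variable. No product of a mediator with an arm or with another mediator is listed.

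**The aim** (Discussion, item (b)). By testing the mediators, the study is to "assist in identifying the mechanisms behind motivational and self-control training components and their interaction on alcohol consumption".

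**The concern.** In mediation terms, the theory puts motivation on the second path, from self-control to drinking. The first path, from training to self-control, is present in everyone who is trained. The listed model has no term that lets the second path differ by simulation arm or by motivation.

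A common-slope model can attribute an interaction to a mediator only if the two components interact on the mediator itself. The theory does not say that they do. If the theory is right, the model finds no mediated interaction and leaves the synergy in the arm-by-arm coefficient. A reader who looks there for the mechanism promised in item (b) gets no answer, or one that points away from the authors' own explanation.

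**Working it through.** **Planned size.** The sample size reproduces and fixes the N used below. With f = d/2, d = 0.56 gives f = 0.28 and d = 0.62 gives f = 0.31. For four groups, alpha 0.05, power 0.80 and three numerator degrees of freedom, the noncentral F gives N = 144 and N = 118 (120 in equal groups), which matches the stated 120 to 144.

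**Algebra.** Let S be simulation, T training, M the state self-control change and Y follow-up drinking.
- Theory: M = aT + error. The slope of Y on M is b1 with simulation and b0 without.
- Total training effect: a·b1 with simulation and a·b0 without. Synergy = a(b1 − b0).
- Listed model: one slope. With equal cells and equal spread of M, it estimates (b0 + b1)/2.
- Mediated part of the interaction = common slope × (S×T effect on M). The theory sets the second factor to 0, so the product is 0.
- The adjusted S×T coefficient is therefore a(b1 − b0), the whole synergy, for any a, b0 and b1.
- With an M×S term, the adjusted S×T coefficient is 0 and the mediated synergy is a × (coefficient of M×S) = a(b1 − b0).

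**Illustration.** The document gives no path values, so these are assumptions in SD units.
- a = 0.6, b1 = −0.6, b0 = 0. Synergy 0.6 × (−0.6) = −0.36. Listed model: slope −0.30, S×T −0.36, mediated part 0. With M×S: S×T 0.
- a = 0.6, b1 = −0.6, b0 = −0.2. Synergy 0.6 × (−0.4) = −0.24. In a large simulation the listed model left −0.238 in S×T; with M×S, 0.004.
- Measured motivation as the moderator: −0.211 of a total of −0.212 stayed in S×T; with M×motivation added, 0.003.
- A case outside the stated theory: simulation also strengthens the training effect on M. From 0.5 to 0.7, the mediated share is (0.30 × 0.2)/(0.7 × 0.6) = 0.06/0.42 = 14%. From 0.4 to 0.8, it is (0.30 × 0.4)/(0.8 × 0.6) = 0.12/0.48 = 25%.

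**Power at the planned size.** I simulated 5,000 trials per row with a = 0.62 (assumed), unit error variances, equal cells, Monte Carlo 95% intervals for products, and arms centred in the mediator regression. Entries are the percentage of trials with a significant result.

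| N | Slope with simulation | Slope without | Pooled indirect effect | Simulation-arm indirect effect | Difference between arms |
|---|---|---|---|---|---|
| 120 | −0.4 | 0 | 49 | 77 | 50 |
| 120 | −0.4 | −0.2 | 80 | 77 | 16 |
| 120 | −0.5 | 0 | 66 | 88 | 67 |
| 120 | −0.5 | −0.25 | 90 | 88 | 23 |
| 144 | −0.4 | 0 | 59 | 85 | 60 |
| 144 | −0.4 | −0.2 | 90 | 86 | 20 |
| 144 | −0.5 | 0 | 76 | 94 | 78 |
| 144 | −0.5 | −0.25 | 95 | 94 | 29 |

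The pooled test loses power only when the slope without simulation is near zero. At half size it does at least as well as the arm-specific test.

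**The case against.** **The common slope is inferred.** The article never says that the slope is equal across arms, it calls the regressions moderated, and a fuller analysis plan may exist. This has some force. But the text lists its terms concretely and names the one interaction that it builds. The point rests on that list set against the stated theory and aim, not on missing detail.

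**The planned predictions concern something else.** Data analysis and Discussion predict mediation of simulation through motivational variables and of training through self-control. The listed terms test those. This stands, and it confines the problem to the interaction part of item (b). Nor does the article say that a remaining arm-by-arm coefficient would be reported as not carried by self-control. A reader might infer that it would be, but the text does not commit to it.

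**Power loss and false attribution.** A reader might go further and conclude that the pooled test loses much power, or credits a mediated effect to participants without simulation who have none. Both need a slope of exactly zero without simulation, and the documents do not support that:
- The sentence after the strict statement softens it to a lower likelihood.
- Recruitment describes the study as an intervention to reduce drinking, and every participant receives a rationale and the guideline limit, so the comparison arms are not unmotivated.
- A medium main effect of training is predicted. A zero slope with a = 0.56 to 0.62 and b = 0.3 to 0.5 would give only ab/2, from 0.56 × 0.3/2 = 0.08 to 0.62 × 0.5/2 = 0.16 SD.

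**Conclusion.** The point holds for the mechanism of the interaction. Under the protocol's own theory, the listed model leaves essentially all of the simulation-by-training synergy in the arm-by-arm term, so it cannot show that self-control carries it. This does not depend on the size of the paths. It rests on two conditions: that no mediator product is added, and that simulation does not change the effect of training on state self-control. If the second fails, part of the synergy is credited to self-control (14% to 25% in the examples above).

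It does not show that the mediation analysis as a whole is invalid. The pooled indirect effect remains a usable average for each component's own mediation, and the primary ANCOVA still tests the interaction on drinking. No single figure for power loss or false attribution should be attached to the plan.

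**What to change.** In Data analysis, keep the planned pooled mediation analysis and make these additions:
- Add to the drinking regression the product of the state self-control change score with the simulation indicator. As a sensitivity analysis, use its product with the motivation change score.
- Report the indirect effect of training through self-control separately for the simulation and comparison arms, with a bootstrap interval for the difference (training effect on self-control × product coefficient).
- In Discussion item (b), limit the claim about the interaction's mechanism to that difference.

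**Cost.** One more parameter, from data already collected, and arm-specific slopes that are less precise than a pooled slope if the slopes are in fact equal. Power for the difference is limited. With a = 0.62 and N = 120 to 144, it is 16% to 29% if the slope without simulation is half that with it. If that slope is zero, power is 50% to 60% at a simulation-arm slope of 0.4 and 67% to 78% at 0.5. The plan should therefore state in advance that a null difference is not evidence against mediated synergy.

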## Discussion

Excessive consumption of alcohol among young people has been recognized as a significant public health issue due to its association with numerous health, social, and economic problems [1]. Undergraduate students tend to be a particularly high-risk group as they frequently engage in risky patterns of alcohol consumption such as binge-drinking [5-7]. Behavioral interventions have been shown to be effective in reducing alcohol consumption in young people e.g., [14,108], but few have reported the theoretical basis of the intervention and its components, tested the independent and interactive effects of the techniques aimed at reducing alcohol consumption, and identified they key mediators of the intervention effects.

The present study aims to conduct a four-week theory-based intervention using leading behavior-change techniques to reduce alcohol consumption at follow-up among undergraduate students. The intervention will adopt motivational and self-control training behavior-change techniques derived from psychological theory and use a randomized-controlled factorial design to examine the unique and interactive effect of each technique in on alcohol consumption. According to theory, we hypothesize that participants receiving both intervention components should exhibit the lowest levels of alcohol consumption at follow-up relative to participants receiving each of the intervention conditions alone and participants receiving neither of the components. In addition, the research will also evaluate the theoretically-relevant mediating variables that explain the effect of the motivational and self-control training intervention components on alcohol consumption. Specifically, we expect the motivational intervention component to be mediated by social cognitive variables including intentions, attitudes, and motivation and the self-control intervention to be mediated by perceived self-control resource availability.

The research will make a unique contribution to knowledge regarding interventions to reduce alcohol consumption and binge drinking occasions in undergraduate students because it will (a) address the limitations of previous research using multiple intervention techniques concurrently by identifying the unique and interactive effects of two isolated and independent intervention techniques (mental simulation and self-control training) to reduce alcohol consumption through the use of a factorial design [20,112]; (b) assist in identifying the mechanisms behind motivational and self-control training components and their interaction on alcohol consumption by testing the effects of key proposed mediating variables [18]; (c) adopt methods that allow for the efficacy of the intervention to be evaluated including written responses to the mental simulation motivational intervention [108] and using an objective means to manage compliance with the programme of self-control resource training via an online training task [85]; and (d) extend knowledge of the causal effects of an intervention aimed at affecting *change* in health behavior through motivational and self-control related variables beyond that which can be inferred from correlational [113] and panel [114] designs.

### Implications

The proposed study has important implications for public health specialists and researchers designing behavioral interventions. The research is relevant to specialists in public health because it will demonstrate the effectiveness of brief interventions including motivational and self-control training components in reducing undergraduate students’ alcohol consumption, the primary outcome variable. This is likely to contribute to initiatives to reduce maladaptive outcomes associated with excessive alcohol consumption in this population. Importantly, the intervention techniques have low response burden and cost and are administered using efficient and effective delivery methods that are readily available including the internet and smartphones. The research is of interest to researchers as it will provide detail on the individual and interactive components of motivational and self-control training on alcohol consumption and also demonstrate the key mediators of the effects. This is important as it will assist in elucidating the ‘active ingredients’ of the intervention and the mechanisms by which they exert their effects.

## Abbreviations

NHMRC: National health and medical research council
FAST: Fast alcohol screening test
